## Abstract

**Background:**

Thromboembolism (TE) is a serious complication in children with acute lymphoblastic leukemia (ALL). The incidence of symptomatic thromboembolism is as high as 14% and case fatality rate of ~15%. Further, development of thromboembolism interferes with the scheduled chemotherapy with potential impact on cure rates. The exact pathogenesis of ALL-associated thromboembolism is unknown. Concomitant administration of asparaginase and steroids, two important anti-leukemic agents, is shown to increase the risk of ALL-associated TE. Dana-Farber Cancer Institute (DFCI) ALL studies reported ~10% incidence of thrombosis with significantly increased risk in older children (≥10 yrs.) and those with high-risk ALL. The majority (90%) of thromboembolic events occurred in the Consolidation phase of therapy with concomitant asparaginase and steroids when high-risk patients (including all older patients) receive higher dose steroids. Certain inherited and acquired prothrombotic defects are known to contribute to the development of TE. German investigators documented ~50% incidence of TE during therapy with concomitant asparaginase and steroids, in children with at least one prothrombotic defect. However, current evidence regarding the role of prothrombotic defects in the development of ALL-associated TE is contradictory. Although thromboprophylaxis can prevent thromboembolism, ALL and it’s therapy can increase the risk of bleeding. For judicious use of thromboprophylaxis, identifying a population at high risk for TE is important. The risk factors, including prothrombotic defects, predisposing to thrombosis in children with ALL have not been defined.

**Methods:**

This prospective, observational cohort study aims to evaluate the prevalence of inherited prothrombotic defects in children with ALL treated on DFCI 05–01 protocol and the causal relationship of prothrombotic defects in combination with patient and disease-related factors to the development of TE. We hypothesize that the combination of prothrombotic defects and the intensive therapy with concomitant high dose steroids and asparaginase increases the risk of TE in older patients and patients with high-risk ALL.

**Discussion:**

The results of the proposed study will help design studies of prophylactic anticoagulant therapy. Thromboprophylaxis given to a targeted population will likely reduce the incidence of TE in children with ALL and ultimately improve their quality of life and prospects for cure.

## Background

Acute lymphoblastic leukemia (ALL), the most common cancer in children, is now curable in over 80% of the children with current aggressive therapy [1, 2]. However, such therapy is associated with significant, sometimes fatal, complications. These therapy-related morbidity and mortality can limit the dose intensification of antileukemic agents and compromise the prospects of cure [3]. Thus, to improve the cure-rates and quality of life of children with ALL, it is important to reduce specific, avoidable therapy-related complications.

Thromboembolism (TE) is one such serious complication in association with ALL therapy in children [4, 5]. Overall TE is rare in general pediatric population with ~0.19 events per 10,000 children [6–8]. In contrast, children with ALL are at much higher risk for TE; reported incidence of symptomatic TE varies from 1% to 14% and that for asymptomatic TE is up to 37% [4, 5, 9]. The majority of the symptomatic TE occur in potentially fatal sites, ***~***50% in the central nervous system (CNS), 2% pulmonary embolism (PE) and 2% in the right atrium [4, 5]. TE including CNS-TE is associated with significant morbidity. In addition, development of TE interferes with the scheduled ALL-therapy; such interruptions are known to compromise cure rates [5, 10]. The average case fatality ratio from TE in children with ALL is 15% [5]. With ~15–20% all-cause mortality in children with ALL; TE may be an important cause of death during ALL-therapy [5, 11].

### Pathogenesis of thromboembolism in children with acute lymphoblastic leukemia

ALL-associated TE is a multifactorial entity [5, 12, 13]***.*** Leukemia, its therapy, and factors inherent to the host seem to collectively contribute to the risk of thrombosis in children with ALL. Central venous line (CVL), a well-known risk factor for TE, is commonly used in children with ALL [4, 5, 9].Children with ALL have evidence of thrombin activation at diagnosis as well as during first several months of therapy [4, 5, 12, 14–20]. Thrombin generation is the central event in the blood clot formation. Figure 1 depicts the role of thrombin in clot formation and possible factors affecting the thrombin generation in association with ALL. Asparaginase (ASP) and steroids form the backbone of most frontline ALL therapy protocols***.*** Available evidence indicate that ASP and steroids induce an acquired prothrombotic state by affecting different hemostatic pathways (outlined in Fig. 1) [12, 21]. ASP, a bacterially derived enzyme, leads to rapid depletion of extracellular pools of asparagine in the body; the resultant inhibition of protein synthesis is responsible for major toxicities of ASP therapy including haemostatic abnormalities [22]. ASP-therapy is shown to causes suppression of natural anticoagulants [antithrombin (AT), protein C (PC) and protein S (PS)] and this reduction, especially AT, is mainly responsible for the ASP-associated prothrombotic state [14, 21].

**Fig. 1 Fig1:**
[figure not shown]
Abbreviations: ASP. Asparaginase; tPA, tissue plasminogen activator; PAI1, plasminogen activator inhibitor 1; Thrombin activation is the central mechanism of hemostasis. Under physiological conditions, blood is maintained in the fluid state by a delicate balance between the pro-coagulant factors [1], natural anti-coagulants [2], and fibrinolytic system which consists of fibrinolytic proteins [3] and inhibitors of fibrinolysis [4]. Thus, an increase in the levels of procoagulant factors combined with reduction in natural anticoagulants or fibrinolytic potential may result in predisposition for thrombosis. ASP and steroids act on different hemostasis pathways as shown above

Steroids are shown to increase coagulation factors II and VIII, and to induce a hypofibrinolytic state with elevation of plasminogen activator inhibitor 1 (PAI1) levels and reduction of α_2_-macroglobulin and tissue plasminogen activator [14, 23–35]. Animal studies have shown a dose dependent effect of steroids on fibrinolytic system [36, 37]. Recent studies showed that concomitant administration of ASP with steroids increases the risk of TE in patients with ALL compared to temporally separate use of ASP and steroids [38–40].

### Effect of congenital or acquired prothrombotic defects in the development of ALL-associated TE

Certain prothrombotic defects increase the risk of TE in adults and children. These include Factor V Leiden (FVL), deficiency of natural anticoagulants (PC, PS and AT), and elevated levels of coagulation factors VIII, IX and XI, [13, 41–43]. In addition, mutations of prothrombin (PT) gene G20210A and methylene tetrahydrofolate reductase (MTHFR) C677T are common and mild risk factors for venous TE in general population [44, 45]. Elevated levels of homocystein (Hcy) and lipoprotein (a) [Lp (a)] are recently identified risk factors for TE [13, 46, 47]. These inherent host factors in the presence of other associated risk factors can increase the risk of TE especially in children with ALL (Table 1) [43]. A multi-center, prospective study of German children receiving therapy on Berlin-Frankfurt-Münster (BFM) ALL protocol 90/95 showed that 48.5% (27/58) children with at least one prothrombotic defect developed venous TE compared to 2.2% (5/231) children without any identified prothrombotic defect (*p* < 0.001) [38].

**Table 1 Tab1:** Potential interactions of thrombophilia and antileukemic agents

Thrombophilia	ALL or Chemotherapeutic agent	Possible interaction
PT gene polymorphism 20210A	ALL	PT mutation may exaggerate ALL-induced thrombin generation
	Corticosteroid	May induce higher levels of PT
MTHFR C677T	Methotrexate	By inhibiting folate pathway induces functional MTHFR deficiency even in heterozygous patients with resultant high Hcy levels
FVL	Asparaginase	By reducing protein C levels may exaggerate the effects of FVL even in heterozygous subjects
Protein C, S and AT deficiency	Asparaginase	By inhibiting protein synthesis results in reduction in Proteins C, S and AT
Elevated pro-coagulant factors VIII:C, IX and XI	Corticosteroid	May induce higher levels of factors VIII:C, IX and XI
Elevated Lp(a) levels	Asparaginase	Lead to mark elevation in Lp(a)

*Abbreviations*: *ALL* acute lymphoblastic leukemia, *PT* prothrombin, *MTHFR* methylene tetrahydrofolate reductase, *Hcy* homocysteine, *FVL* Factor V Leiden, *AT* antithrombin, *FVIII:C* Coagulation factor VIII:C, *Lp(a)* Lipoprotein a

By alterations in hemostatic proteins ALL and it’s therapy may exacerbate the deleterious effects of inherent thrombophilia, even for those factors which otherwise pose mild risk for TE in general population (namely PT and MTHFR mutations). Table 1 outlines the potential interaction of inherent thrombophilia with ALL and commonly used antileukemic agents.

Although association of antiphospoholipid antibodies (APLA) with TE is well known, it is not very well studied in children with ALL. In a multicenter, prospective Prophylactic Antithrombin Replacement in Kids with Acute Lymphoblastic Leukemia Treated with Asparaginase (PARKAA) study, 8 of 60 (13%) children with ALL had APLA; four of them developed CVL related TE [48]. Although small, this study highlights the potential importance of thrombotic risk posed by APLA in children with ALL.

### Thrombophilia as a risk factor for ALL-associate TE

Certain ethnic groups seem to have high prevalence of thrombophilia; 43% of Arab and Jewish children with ALL are reported to have inherited thrombophilia [49]. Very few studies have evaluated prevalence of thrombophilia in children with ALL [38, 39, 48–50] and only 3 studies evaluated the impact of thrombophilia on the development of TE [38, 39, 48]. These studies reported wide variability in prevalence of thrombophilia (18% to 40%) and frequency of TE in children with ALL and thrombophilia (0 to 48%); probably related to the different ethnicity of the population studied and marked variability in the extent of thrombophilia tested. Further, use of different therapy protocols and small sample size make it difficult to interpret the data.

Since the prevalence of thrombophilia varies with ethnicity and different therapy protocols are likely to have different effects on the hemostatic system, the results of the German studies cannot be generalized to North American children treated on different ALL protocols [38, 39].The prevalence of thrombophilia and its relationship to symptomatic TE in North American children with ALL is largely unknown.

### Relevance and importance of the proposed study: preliminary results of DFCI studies

TE is a significant problem in children receiving therapy on DFCI ALL protocols. Pilot data from Canadian institutions showed 11% prevalence of symptomatic TE in children receiving therapy on DFCI ALL protocols [51]. Older age (≥ 10-years) and high-risk (HR) disease are important risk factors for development of TE; older patients (≥ 10-years) compared to younger patients (44% vs. 4%, *p* < 0.0001) and patients with HR ALL compared to standard-risk (SR) ALL (26% vs. 2%) had higher prevalence of TE (*n* = 91) [51].

The effect of older age and HR ALL on the risk of symptomatic TE was confirmed in Consortium-wide review of earlier protocols; overall incidence of TE in children ≥10 years was 12% compared to 2% in children <10 years of age (*p* < 0.0001) [DFCI ALL studies 91–01 and 95–01 (*n* = 906)] and in children with HR ALL was 17% compared to 1.5% in children with SR ALL (*p* = 0.005) [DFCI 20–01(*n* = 118)]. Of note, data on TE was not consistently collected on earlier DFCI protocols.

The etiology of the increased susceptibility of older and HR ALL patients to TE is unknown, it is likely related to the therapy they receive. Majority of the episodes of TE in patients treated on DFCI ALL therapy protocols occurred during Consolidation phase where ASP and steroids are given concomitantly. Moreover during this phase, HR patients (including all patients ≥10 years) receive thrice as much steroids as SR patients [52]. Compared to the contemporary therapy protocols, DFCI ALL protocols use higher cumulative doses of steroids and ASP.

In contrast to BFM studies, our data showed that the dose, but not the type, of steroid used with ASP significantly altered the risk of TE on DFCI ALL-protocols. Patients receiving high-dose steroids were at significantly higher risk of TE (18.2% Vs 2.7% in patients with lower dose steroids; *p* = 0.004) [53, 54].

Our preliminary studies indicate that children who develop TE are more likely to have adverse outcome from ALL compared to those who do not develop TE. Silverman et al., on DFCI 91–01 study showed that early (< 25 weeks) discontinuation of ASP-therapy adversely affected 5-year event free survival (EFS) (73% vs. 90%; *p* < 0.01); CNS event or non-CNS-TE was responsible for early discontinuation of ASP in 20% of patients [10]. We observed 27% (3/11) mortality in children with ALL and TE compared to 6% (5/84) in children with ALL without TE (*p* = 0.048; 95% CI -5.5, 48.1).

There is no information about thrombophilia in patients treated on DFCI studies. At McMaster University, 10 of 12 patients with ALL and symptomatic TE were evaluated for prothrombotic defects; 9 had abnormal thrombophilia profile and 6 patients had >1 defect. Nine patients had increased levels of factor VIII:C (mean 3.2 U/mL; range 2.11–5.8); 3 patients had elevated fasting Lp (a) levels, one each had increased fasting Hcy level, reduced PS levels, AT deficiency and one was heterozygous for MTHFR C677T. Although the sample size is small and the prothrombotic work-up was performed after the detection of TE, this data strongly support detail evaluation of inherited and acquired prothrombotic defects as a potential risk factor for ALL-associated TE.

In summary, TE is a significant complication in children with ALL. Prothrombotic defects are shown to be prevalent in ~20% of children with ALL. Leukemia and its therapy can potentially exacerbate the deleterious effects of prothrombotic defects even in heterozygous individuals. However, the extent of the risk, if any, predisposed by prothrombotic defects in the development of TE in children with ALL (especially in relation with ALL-therapy) is unknown. Hence we propose a thrombophilia study within the context of DFCI ALL 05–01 randomized controlled trial (RCT). The proposed thrombophilia study will evaluate the role of prothrombotic defects in the development of TE as well as the interaction, if any, of these defects with patient (e.g. age), disease (e.g. risk-categorization) and therapy (e.g. the type of ASP) variables.

## Methods/trial design

### Scientific questions

The primary question is do identified congenital and acquired prothrombotic defects increase the risk of symptomatic TE in children with ALL receiving therapy on DFCI ALL 05–01 protocol? The secondary question is what other baseline and time-dependent factors increase the risk of clinically symptomatic TE in children with ALL receiving therapy according to DFCI ALL 05–01 protocol?

### Hypotheses

Primary hypothesis is that children with one or more prothrombotic defect/s are at increased risk for development of symptomatic TE during ALL-therapy on DFCI ALL 05–01 protocol compared to those without any identifiable prothrombotic defect. Secondary hypothesis is that older age of the patient (compared to younger age), HR or very high risk (VHR) ALL (compared to SR ALL), and therapy with *E. coli* ASP (compared to Pegylated (PEG) ASP), either alone or in combination with one or more prothrombotic defect, increase the risk of symptomatic TE in children on DFCI 05–01 ALL-therapy protocol.

### Overall objective

To explore the relationship of inherited and acquired prothrombotic defects with the development of symptomatic TE in children with ALL treated on DFCI ALL 05–01 protocol.

### Specific aims

#### Primary Aim

To compare the risk of development of symptomatic TE in children **with** or **without** prothrombotic defect receiving therapy on DFCI ALL 05–01 protocol.

#### Secondary Aims

To evaluate the effect of age of the patient (≥ 10 years versus <10 years), risk categorization of ALL (HR/VHR ALL versus SR ALL), baseline laboratory features (white blood cell counts, blast count and platelet count), type of ASP used (*E. coli* versus PEG), phase of therapy (Consolidation II versus other), either alone or in combination with any known prothrombotic defect/s, on the risk of development of symptomatic TE in children receiving therapy on DFCI ALL 05–01 protocol. (Since almost all our patients have CVL, we will not be able to evaluate the effect of CVL in relation with other factors).To develop a predictive model to identify children with ALL at high risk for TETo determine the prevalence of inherited and acquired prothrombotic defects in children newly diagnosed with ALL

### Research design

This is a prospective analytical cohort study conducted within the context of DFCI ALL randomized controlled trial 05–001. Figure 2 outlines the design of proposed thrombophilia study. DFCI ALL 05–001 study was opened for patient enrollment in three Canadian and six US institutions in June 2005. The DFCI 05-001RCT aims to compare the efficacy and toxicity of two ASP preparations namely PEG and *E. coli* ASP. The detail therapy plan and ALL risk category is described previously [55].

**Fig. 2 Fig2:**
[figure not shown]
Overview of the study and patient flow

### Patient population

#### Study sites

This study was planned to be conducted at three tertiary care pediatric oncology centers within DFCI Consortium. However due to logistic issues the third site could not join and the study was activated at two sites: McMaster University, Hamilton and Hospital Ste. Justine, Montreal.

#### Patient eligibility

Inclusion Criteria: All children (between ages 1 to 18 years) newly diagnosed with ALL at the participating institutions and enrolled on DFCI ALL 05–01 study were eligible for the proposed study.

Children <12 months and >18 years of age and those with relapsed ALL (since they are not eligible for DFCI 05–01 study) and patients unable, or unwilling, to provide written informed consent (and/or assent) were excluded from the proposed thrombophilia study.

#### Procedure for patient identification and obtaining consent

Newly diagnosed ALL patients were identified through Pediatric Oncology service. Study staff reviewed patients’ records to determine eligibility for the proposed study. Eligible patients were approached, prior to starting ALL therapy, for informed consent. Reasons for non-participation were recorded for all screened patients.

### Observations

#### Dependent variable

Development of symptomatic TE in any location while receiving therapy on DFCI ALL 05–01 study. *Symptomatic TE* is defined as any objectively confirmed arterial or venous TE which was discovered as a result of investigations prompted by typical clinical symptoms (as outlined in Table 2). Screening for *asymptomatic* TE was not performed.

**Table 2 Tab2:** Definition of symptomatic TE and preferred diagnostic evaluation

	Site	Likely clinical signs and symptoms	Diagnostic method/s
CNS	Arterial ischemic stroke +/− hemorrhage	Unexplained headaches, vomiting, visual problems, or neurological deficits, seizure, drowsiness or any change in mental status	MRI/MRA Angiogram
	Sinovenous thrombosis (SVT)		MRI /MRV CT venogram
PE	Pulmonary vasculature	Respiratory problems (shortness of breath, tachypnea, dyspnea) hypoxia, chest pain, syncope “Unexplained pneumonia”	V/Q scan Spiral CT Pulmonary angiogram
DVT	Upper venous system	Swelling, pain, tenderness, erythema, dilated vessels	Bilateral venogram is “gold standard” for diagnosis especially for subclavian/brachial vessels ^a^Doppler USG sufficient for jugular vein MRV Recommend ECHO to evaluate RA
	Lower venous system		^a^Doppler USG to evaluate all sites Venogram is still the gold standard
Cardiac	Right atrial (RA)	CVL malfunction, sepsis, congestive heart failure	ECHO
CVL related	Asymptomatic CVL tip thrombi **ONLY if** the catheter tip is in RA	-	ECHO Linogram Venogram
	**Only** symptomatic CVL TE will be considered significant	Swelling, pain, tenderness, erythema, dilated vessels, CVL malfunction requiring revision or renewal, headache, swelling of face	Linogram +/− venogram &/or ^a^Doppler USG depending upon the site of thrombosis

In the presence of TE at one site recommend evaluating other sites (especially if anatomically related e.g. jugular vessels in presence of SVT) for associated asymptomatic TE, if possible

*TE* thromboembolism, *CNS* central nervous system, *MRI* Magnetic resonance imaging, *MRV* Magnetic resonance venogram, *MRA* Magnetic resonance arteriogram, *PE* pulmonary embolism, *V/Q* scan ventilation/perfusion scan *CT* computerized tomogram, *DVT* deep venous thrombosis, *USG* ultrasonogram, *CVL* central venous line

^a^Detection of echogenic material within the lumen of a vein on a gray scale and presence of partial or complete absence of flow by pulse wave or color Doppler ultrasonography

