### Outcomes

#### Primary outcome

Diagnosis of symptomatic TE in any location while on active ALL-therapy.

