#### Justification for inclusion of symptomatic TE

Clinical significance of asymptomatic TE detected by screening methods is so far unknown. Further, by inclusion of only symptomatic and objectively confirmed TE, we will avoid ambiguity over diagnosis, and thus, reporting of TE. Also the inclusion of only symptomatic TE will avoid invasive (e.g. venography) and non-invasive (e.g. ultra-sonography) tests to screen for asymptomatic TE. This, we hope, will improve patient and physician compliance and participation in the study.

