#### Criteria for diagnosing symptomatic TE

Objective testing must be done to confirm suspected thrombotic events in symptomatic patient (Details in Table 2). Acceptable objective tests for diagnosis of CNS TE: cerebral angiographies, contrast enhanced magnetic resonance imaging (MRI), MR arteriography (MRA) or MR venography (MRV); deep venous thrombosis (DVT) include: venography, Doppler ultrasonography (USG), contrast enhanced computerized tomography (CT), MRV; for PE: pulmonary angiography, ventilation/perfusion (V/Q) scan or spiral CT scan; and for right atrial TE: echocardiography (ECHO). DVT was diagnosed by detection of echogenic material within the lumen of a vein on a gray scale and presence of partial or complete absence of flow by pulse wave or color Doppler ultrasonography or if venography or contrast enhanced CT shows a persistent intraluminal filling defect [9, 56, 57]. CNS-TE was diagnosed if imaging modalities showed intraluminal arterial or venous filling defect/s with or without associated cortical changes. PE was confirmed with intraluminal filling defect or abrupt cut-off or non-filling of an arterial segment on either pulmonary angiograpghy or spiral CT scan or a high probability V/Q scan.

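### Table 2 lists an asymptomatic right-atrial catheter-tip thrombus under the primary outcome of symptomatic TE, so the same child can be an event or a non-event

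*Protocol article*

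**What the plan says.** All references are to the protocol article.

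- **Primary outcome:** "Diagnosis of symptomatic TE in any location while on active ALL-therapy".
- **Dependent variable (prose):** the TE must be objectively confirmed and "discovered as a result of investigations prompted by typical clinical symptoms (as outlined in Table 2"). The same paragraph adds: "Screening for *asymptomatic* TE was not performed".
- **Table 2:** its title is "Definition of symptomatic TE and preferred diagnostic evaluation", so it belongs to the outcome definition. The first of its two CVL-related rows reads "Asymptomatic CVL tip thrombi ONLY if the catheter tip is in RA". The symptom cell holds a dash, and the tests are echocardiography, linogram and venogram. The second row begins with a bold Only and continues "symptomatic CVL TE will be considered significant".
- **Justification for inclusion of symptomatic TE:** "by inclusion of only symptomatic and objectively confirmed TE, we will avoid ambiguity over diagnosis". The section on internal validity repeats this and sends suspected events to an independent adjudication committee.
- **Criteria for diagnosing symptomatic TE:** objective testing is required to confirm suspected events in a symptomatic patient.

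**The concern.** The condition in the first CVL row reads naturally as a condition for counting: a tip thrombus without symptoms qualifies when the tip lies in the right atrium. It cannot be a restatement of symptomatic right-atrial thrombosis, because Table 2 has a separate cardiac row for that site with its own symptoms.

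Two things are at stake.

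- **Ascertainment.** The symptom trigger is what makes case-finding uniform across children. A tip thrombus without symptoms enters only if the child had an echocardiogram or line study for another reason. The Secondary Aims say that almost all patients have a CVL, so nearly the whole cohort is exposed to this.
- **Classification.** The primary analysis in Table 3 is Fisher's exact test on a binary outcome with few events. Two adjudicators, each following one of the two rules, would code the same child differently, and that child moves the test directly.

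**Working it through.** **1. The two rules side by side, for a child whose only finding is an asymptomatic RA-tip thrombus**

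| Source | Event? |
|---|---|
| Dependent variable, prose (symptom-prompted investigation) | No |
| Table 2, first CVL row | Yes |
| Table 2, second CVL row | No |
| Primary outcome | No |
| Justification for inclusion of symptomatic TE | No |
| Criteria for diagnosing symptomatic TE | No |
| Internal validity | No |

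Adjudication does not settle the matter, because the article does not say which rule the committee applies.

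**2. Reproducing the plan's power figure**

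Inputs from Sample size: 150 children (30 with and 120 without a defect), overall TE incidence 11%, defect prevalence 20%, difference 25 points, two-sided α = 0.05.

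- Risk without a defect: 0.11 − 0.20 × 0.25 = 0.06. Risk with a defect: 0.06 + 0.25 = 0.31.
- Expected events: 150 × 0.11 = 16.5.
- Exact Fisher power at 30 versus 120: 92.2%.
- If 11% is read instead as the risk without a defect (36% versus 11%), the power is 84.5%.

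Both agree with the stated figure of more than 80%. The revised plan (Study progress and modification to study protocol: 15% incidence, 131 patients) implies 131 × 0.15 ≈ 20 events, which is the same order.

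**3. One child at the margin (illustrative tables)**

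| With defect | Without defect | Fisher p |
|---|---|---|
| 6/30 | 8/120 | 0.036 |
| 6/30 | 9/120 | 0.080 |
| 7/30 | 10/120 | 0.046 |
| 7/30 | 11/120 | 0.054 |

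In each pair, one asymptomatic tip thrombus counted in the group without a defect takes p from below to above 0.05.

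**4. Effect on power under an assumed rate**

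The article gives no rate. Assume that a fraction *a* of otherwise event-free children have such a thrombus detected and counted, unrelated to defects. Each risk *p* becomes *p* + (1 − *p*)*a*.

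| *a* | Risks | Difference (points) | Events added | Share of all events | Fisher power |
|---|---|---|---|---|---|
| 0 | 31.0% vs 6.0% | 25.0 | 0 | 0 | 92.2% |
| 1% | 31.7% vs 6.9% | 24.75 | 1.3 | 7% | 90.2% |
| 2% | 32.4% vs 7.9% | 24.5 | 2.7 | 14% | 88.2% |
| 5% | 34.5% vs 10.7% | 23.75 | 6.7 | 29% | 81.8% |
| 6% | 35.1% vs 11.6% | 23.5 | 8.0 | 33% | 79.6% |

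**The case against.** **One row stands against many statements.** Outside that cell the rule is consistent, and a reader could say that the prose governs. This is fair as to how much text lies on each side. But the prose points to Table 2, and the table's title calls it the definition, so the row cannot be ignored.

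**The row may be a deliberate exception.** The Background names the right atrium among potentially fatal sites, so a general rule with one bounded exception is plausible. This stands: the documents do not prove that the row is a slip. They do not state it as an exception either, and the second CVL row allows none.

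**The numerical effect is modest.** This also stands. The 2% to 5% rate is an assumption, and it has to be a rate of detected thrombi in a study without screening. At those rates power stays above 80%. Additions unrelated to defects dilute the contrast slightly and do not create a false association. Detection that differs by defect status has not been shown.

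**Two stronger readings a reader might infer are not supported.**

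- *That Table 2's advice to look for associated asymptomatic TE at other sites adds primary events.* That advice applies once a TE has been found at one site. The child is already an event, so the binary outcome cannot change.
- *That the differing test lists put the CNS events in doubt.* Table 2 includes CT venogram for sinovenous thrombosis, whereas the criteria section has "Acceptable objective tests for diagnosis of CNS TE: cerebral angiographies, contrast enhanced magnetic resonance imaging (MRI), MR arteriography (MRA) or MR venography (MRV") without it. Linogram is likewise in Table 2 only. But the criteria section refers to Table 2 for details, and its CNS criterion is an intraluminal filling defect on imaging, whatever the modality. Contrast CT for deep venous thrombosis appears only in the criteria section, which is no conflict: a test can be acceptable without being preferred. What remains is editorial.

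**Conclusion.** The conflict holds and rests on the text alone. Table 2 admits an asymptomatic RA-tip thrombus to an outcome that its own next row, the prose definition and four other sections limit to symptomatic TE, and nothing in the article says which rule prevails.

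The number of children affected is unknown. With about 16 expected events, one reclassified child can decide whether the primary test is significant; the tables showing this are constructed examples. The loss of power, from 92% to 88% or 82%, depends on the assumed 2% or 5% rate and on thrombi unrelated to defects. It does not bring the study below its stated 80%. The reason to act is that the primary outcome must classify each child in one way, not that power is lost.

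**What to change.** Reconcile the passages before the final analysis; the article says that the study is still in follow-up.

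1. State in the outcome definition whether an asymptomatic RA-tip thrombus is a primary event. The resolution consistent with the stated outcome is that it is not, and that such findings are recorded as a separate item.
2. If the row is a deliberate exception, say so in the prose definition and in Primary outcome, amend the second CVL row to match, and report the primary comparison with and without these events.
3. Give the adjudication committee that single rule, and have any event already classified under the other rule reviewed again.
4. Editorial: make the test lists agree, either by adding CT venogram and linogram to the acceptable tests in Criteria for diagnosing symptomatic TE or by removing them from Table 2.

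The cost is a wording change and a re-check at adjudication, with possibly a few fewer primary events if these thrombi are not counted.
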